## **Study outcomes**

### *Primary Endpoint*

The primary endpoint is the proportion of patients progressing to severe respiratory failure (Brescia-COVID  $\geq 2$ ), ICU admission, or death.

### *Secondary endpoints*

1. Time to progression to severe respiratory failure
2. Time to reduction of supplemental oxygen requirements
3. Time to non-invasive or invasive ventilation.
4. Proportion of patients with at least 1 point progression in the 7-point ordinal scale from randomization up to day 15

Ordinal scale:

1. Not hospitalized, no limitations on activities.
  2. Not hospitalized, limitation on activities.
  3. Hospitalized, not requiring supplemental oxygen.
  4. Hospitalized, requiring supplemental oxygen.
  5. Hospitalized, on non-invasive ventilation or high flow oxygen devices or oxygen mask with reservoir bag.
  6. Hospitalized, on invasive mechanical ventilation or ECMO.
  7. Death.
5. Rate of hospital discharge
  6. Duration of hospitalization
  7. Mortality rate and survival time.
  8. Rate of ICU admission
  9. Changes in serum levels of inflammatory cytokines.
  10. Proportion of patients showing more than >1 organ failure, e.g. cardiovascular, liver and kidney failure
  11. Safety and tolerability – Adverse event: The occurrence of treatment adverse events (AEs), serious AEs (SAEs), and laboratory abnormalities in the following, but not limited to, parameters: acute phase reactants CRP and ESR, complete blood count (including ANC and platelets), liver enzymes (ALT, AST and AP), and lipid levels, (time frame: up to day 15)

### ***Calendar of Evaluation of Trial Variables***

Safety will be evaluated through the collection of all AE for up to 28 days.

The Principal Investigator may decide to conduct interim analysis of study data at any time, even while some subjects may remain in follow-up. The timing of data analysis is the prerogative of the Principal Investigator, regardless of continuing long-term follow-up of study subjects.

## 9. PHARMACOVIGILANCE/ADVERSE EVENTS/SAFETY

All adverse events will be recorded in the CRF and graded according to the NCI-CTC v.5.0 (See Appendix 4).

### ***Definitions***

Adverse Event is defined as any event that results in worsening of the health of the subject of the clinical trial, regardless of relationship to the experimental therapy. It can be any symptom, sign, illness or experience, including abnormal results of diagnostic procedures, that develops or worsens in severity during the course of the study.

Any medical condition that is present at the time that the subject is screened will be considered as baseline and not reported as an AE. However, if the severity of any pre- existing medical condition increases, it should be recorded as an AE.

Given the nature of severity of the underlying illness, subjects will have many symptoms and abnormalities in vitals and laboratory. Only Grade 3 and 4 AEs will be captured as AEs in this trial, according to the following classification:

- Mild (Grade 1): Events that are usually transient and may require only minimal or no treatment or therapeutic intervention and generally do not interfere with the subject's usual activities of daily living.
- Moderate (Grade 2): Events that are usually alleviated with additional specific therapeutic intervention. The event interferes with usual activities of daily living, causing discomfort but poses no significant or permanent risk of harm to the research subject.
- Severe (Grade 3): Events interrupt usual activities of daily living, or significantly affects clinical status, or may require intensive therapeutic intervention. Severe events are usually incapacitating.
- Very severe (Grade 4): Events that are potentially life threatening.

Serious Adverse Event are defined as any AE (or adverse reaction) that in the view of either the investigator or the sponsor, it results in any of the following outcomes:

- Fatal
- Life-threatening\*
- Requires or prolongs hospital stay
- Results in persistent or significant disability or incapacity
- A congenital anomaly or birth defect

The concept "life-threatening" means that in the opinion of the investigator, the patient is in real danger of death in the AE situation; it does not mean that the AE could have caused death if it would have been more intense.

Any AE that constitute an important medical event, will be treated as a SAE regarding notification procedures. Important medical events are those that may jeopardize the subject, and may require intervention to prevent one of the other serious outcomes noted above. All proven incidents of transmission of an infectious agent through the delivery of experimental therapy will also be

reported as SAEs.

Adverse reaction is any untoward medical occurrence associated to the administration of a research drug. It is different to an AE in that, in the AR, there is a suspicion of causal relationship between the research drug and the effect.

For each reported adverse event, the PI or designee must assess the relationship of the event to the study product using the following guideline:

- **Related** – The AE is known to occur with the study intervention, there is a reasonable possibility that the study intervention caused the AE, or there is a temporal relationship between the study intervention and event. Reasonable possibility means that there is evidence to suggest a causal relationship between the study intervention and the AE.
- **Not Related** – There is not a reasonable possibility that the administration of the study intervention caused the event, there is no temporal relationship between the study intervention and event onset, or an alternate aetiology has been established.

The relationship or causality of the AE to sarilumab therapy will be determined by the PI of the center, or the person in whom she/he delegates.

#### Suspected Unexpected Serious Adverse Reaction (SUSAR)

A SUSAR is a serious adverse reaction (SAR) as noted above, that is also unexpected. Unexpectedness is defined as an adverse event in which the nature, severity, specific or consequences have not been previously observed or noted in the reference information for the drug or that has been noted in the same drug class. An ADR with a fatal outcome is considered unexpected.

#### ***Registry of AE***

All AE will be documented, including the ones observed during clinical visits and the ones reported by the patient. AEs will be documented throughout the duration of the trial. The patient should be asked about possible AEs in the time between clinical visits.

All AE will be documented in the CRF and in the medical records.

All AE will be followed until resolution, until 15 days after the administration of the first dose of sarilumab (V1), or until toxicity is considered non-reversible or is grade 1.

#### ***SAE that do not require expedited notification***

The patients who will participate in this study have a poor prognosis, with the possibility of death due to the disease. This possible progression is included in the primary endpoint, so it will not be necessary to report deaths as SAE in this study.

This event will be documented in the medical history and in the CRF of the patient. The rest of the SAE will be reported by the investigator following the expedited report procedure as follows.

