##### *Objectives and endpoints*

Table 1 - Objectives and endpoints

| OBJECTIVES                                                                                                                                                                     | ENDPOINTS AND OUTCOME MEASURES                                                                                                                                                                 |
|--------------------------------------------------------------------------------------------------------------------------------------------------------------------------------|------------------------------------------------------------------------------------------------------------------------------------------------------------------------------------------------|
| PRIMARY                                                                                                                                                                 |                                                                                                                                                                                                |
| Evaluate the efficacy of an early intervention with sarilumab in COVID-19 infected patients with pneumonia and regular oxygen supplement requirements (Brescia-COVID 1) | The primary endpoint is the proportion of patients progressing to severe respiratory failure (Brescia-COVID $\geq 2$ ), ICU admission or death from randomization up to day 15th of follow-up. |
| SECONDARY                                                                                                                                                               |                                                                                                                                                                                                |

---

**Evaluate effects of efficacy of an early intervention with sarilumab on secondary efficacy endpoints as compared to standard of care as assessed by:**

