**To evaluate safety of sarilumab as compared to SOC**

Safety through day 29

- Cumulative incidence of serious adverse events (SAEs)
- Cumulative incidence of Grade 3 and 4 adverse events (AEs).

Serious adverse events (SAEs).  
Grade 3 or 4 Adverse events (AEs).

|                                                                                                                                                   |                                                                                                                                    |
|---------------------------------------------------------------------------------------------------------------------------------------------------|------------------------------------------------------------------------------------------------------------------------------------|
| To evaluate differences in the effect of sarilumab on the serum levels of inflammatory cytokines in patients infected with COVID-19.       | Changes in serum level of CRP, IL-6, lymphocyte count, neutrophils count, d-dimer, LDH, ferritin, coagulation tests                |
| To evaluate differences in the proportion of patients showing more than >1 organ failure, e.g. cardiovascular, liver and kidney failure | Patients showing more than >1 organ failure through day 15                                                                         |
| To identify prognosis factors of sarilumab efficacy related to laboratory parameters or disease features                                   | Focused medical history, demographic characteristics, COVID-19 history, concomitant medication, and laboratory disease parameters. |

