#### *Serious Laboratory Abnormalities*

Any laboratory abnormality meeting the regulatory definition of "serious" must be recorded both on the adverse event case report form and the Serious Adverse Event Form. If a subject experiences a serious toxicity or dies, the local and national required regulatory authorities will be notified within 24 hours of awareness of the event, as required.

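### The exemption of deaths from SAE reporting is justified for COVID-19 deaths but written for all deaths, so it conflicts with the protocol's own fatal-event rules and leaves the SAE endpoint with two readings

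*Protocol*

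**What the plan says.** The rule is in Protocol section 9, under the heading on SAEs that do not need expedited notification. It notes the poor prognosis and the chance of dying from the disease, says this progression belongs to the primary endpoint, and concludes "so it will not be necessary to report deaths as SAE in this study". Deaths go into the medical history and the CRF; the remaining SAEs go through the expedited procedure.

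Other parts of the Protocol bear on this:

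- **Section 9, Definitions.** "Serious Adverse Event are defined as any AE (or adverse reaction) that in the view of either the investigator or the sponsor" leads to a listed outcome; fatal is the first on that list.
- **Section 9, Definitions (grades).** "Only Grade 3 and 4 AEs will be captured as AEs in this trial". The grade list stops at potentially life-threatening.
- **Section 9, Definitions (causality).** "For each reported adverse event, the PI or designee must assess the relationship of the event to the study product".
- **Section 9, SUSAR definition.** "An ADR with a fatal outcome is considered unexpected".
- **Section 9, Urgent or expedited notification of SUSAR.** A fatal SUSAR is due within 7 days of the sponsor learning of it.
- **Section 9, Serious Laboratory Abnormalities.** "If a subject experiences a serious toxicity or dies, the local and national required regulatory authorities will be notified within 24 hours", qualified at the end of the sentence by the words as required.
- **Section 4, Table 1.** One safety outcome, followed to day 29, is "Cumulative incidence of serious adverse events (SAEs".
- **Section 7, Potential Risks.** Serious infection is the first risk listed for sarilumab.

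**The concern.** The sentence that sites will act on is wider than the argument for it. Inclusion in a composite efficacy endpoint can justify sparing sites expedited reports of expected disease deaths. It does not justify sparing them a report of a death that may be due to the drug, because the primary endpoint counts a death without judging its relation to sarilumab.

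Two things are at stake. The first is pharmacovigilance: the SAE form is the usual way a fatal event reaches the people who must decide whether it is a SUSAR, and the rule waives it for every death. The second is the safety endpoint: the SAE incidence can be tabulated with deaths (by the definition) or without them (by the exemption), and the Protocol does not say which.

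**Working it through.** The Protocol gives no figure on this point, so there is none to reproduce. The check compares the clauses and follows a case through them.

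**1. Reason against rule.** The premise names only death from the disease. The conclusion names deaths, with no limit by cause. The limit in the premise is not carried into the rule.

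**2. A death from infection on sarilumab, with no SAE form filed before death.**

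- By the Definitions it is an SAE, because the outcome is fatal.
- By the exemption it need not be reported as one.
- If related to sarilumab, it is a fatal adverse reaction and so unexpected by rule. Serious, related and unexpected together make a SUSAR, due within 7 days of sponsor knowledge.
- The form that normally gives the sponsor that knowledge, described under Reporting of SAEs and due within 24 hours, is the one the exemption waives.

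The exemption and the SUSAR rules therefore pull in opposite directions for exactly the deaths where reporting matters most.

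**3. Heading against text.** The heading concerns expedited notification only, which suggests that deaths remain SAEs and merely travel by a slower route. The sentence says they need not be reported as SAEs. This gives two readings of the SAE incidence in Table 1:

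| Patient | Deaths counted | Deaths not counted |
|---|---|---|
| Infection reported as an SAE, then death | counted | counted |
| Death is the first and only serious event | counted | not counted |
| Serious event, survives | counted | counted |

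The readings differ by the number of patients in the second row. That number is the deaths per arm multiplied by the share with no earlier SAE report. The Protocol gives neither quantity, so no size follows.

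**4. The Grade 3 and 4 total.** It does not settle the matter, since the grades captured include none for a fatal event.

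**5. What is still captured.** Deaths are entered in the CRF. Table 1 records date and cause of death. The schedule of activities checks mortality up to the 28-day visit. Mortality and survival time are secondary endpoints in section 8.

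**The case against.** The strongest defence is that the paragraph should be read as a whole. Its heading is about expedited notification, its premise is disease death, it goes on to speak of a single kind of event, and its closing reference to the remaining SAEs implies that deaths are still SAEs. On that reading only the routing changes, and Table 1 counts SAEs by the definition, deaths included. Nothing says the endpoint is tallied only from expedited forms, and the data needed to include deaths are in the CRF.

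Much of this stands. The narrower intent is plausible and the data exist. But the operative words are not limited to COVID-19 deaths, and a site that takes them literally has complied with the Protocol. An intent that must be inferred against the text should be written down.

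A reader might also infer three stronger claims, which the Protocol does not support:

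- **That a fatal adverse reaction has no route to recognition.** The Definitions end by giving the site's principal investigator the task of determining causality. Section 12 makes the principal investigator responsible for urgent reporting of SAEs and SUSARs within 24 hours. The sponsor's 7-day clock runs from knowledge, which a CRF entry could supply. The route is weakened, not absent.
- **That late deaths form a special gap.** Table 1 ends the primary endpoint at day 15 ("ICU admission or death from randomization up to day 15th of follow-up"), while safety runs to day 29. But Reporting of SAEs already limits every SAE arising more than 15 days after the end of experimental therapy to events judged causal or medically important, so the narrowing is not peculiar to deaths. The endpoint window itself varies: the synopsis and section 8 give none, and section 10 names day 7.
- **That the 24-hour notification clause flatly contradicts the exemption.** It mentions a subject who dies, but it sits under serious laboratory abnormalities and applies as required. It needs aligning; it is not the main conflict.

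**Conclusion.** The point holds as a defect in a stated rule. The exemption reaches deaths that its own reason does not cover. It conflicts with the SAE definition and undercuts the fatal adverse reaction and 7-day SUSAR rules. It also leaves open whether deaths count in the SAE incidence.

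It does not mean that deaths are lost or that mortality by arm cannot be compared. Nor does it mean that a fatal infection will be missing from the SAE count, only that it can be. An infection reported earlier as life-threatening or as prolonging the stay is counted on either reading. A reader might want a figure for the undercount, but any such figure would need an assumed mortality and an assumed share of deaths without an earlier SAE report, and the Protocol states neither. The direction of any difference between arms is likewise unknown.

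The conclusion rests on the wording alone and assumes only that some sites will follow the exemption as written. It should be corrected, but it does not affect the primary analysis.

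**What to change.** - **Section 9, the exemption.** Limit it to expedited notification of deaths the investigator judges due to COVID-19 progression and not related to sarilumab. Record every death with its cause and the causality assessment set out in Definitions. Send all other deaths through Reporting of SAEs and, where they qualify, the SUSAR procedure.
- **Section 4, Table 1.** State that SAE incidence includes deaths of any cause through day 29.
- **Section 4, Table 1, and section 9, Definitions.** Add fatal events to the Grade 3 and 4 events captured.
- **Section 9, Reporting of SAEs.** Align the 15-day limit with the day-29 safety window. Otherwise the endpoint would hold all late deaths but only those late non-fatal SAEs judged related or important.
- **Section 9, Serious Laboratory Abnormalities.** Make the clause on deaths agree with the revised exemption and the SUSAR timelines.

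The cost is wording plus one extra form per death; cause of death is already collected. The Protocol gives no mortality figure. If 3% to 10% of the 200 patients died (an assumption), that would be 200 × 0.03 = 6 to 200 × 0.10 = 20 forms. The downside is that the exemption from expedited notification would rest on attribution by investigators who know the treatment. The SAE count would not, because it would include every death whatever its attribution.

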#### ***Procedure of notification***

##### ***Reporting of SAEs***

In case of occurrence of a SAE that must be reported to pharmacovigilance, a SAE Serious Adverse Events Reporting Form must be completed and signed by the investigator within 24 hours. The investigator will keep a copy of this SAE form on file at the study site.

When additional information about the SAE becomes available, or when the SAE is resolved, or when any change is unexpected, the investigator must provide further information in the form of a written narrative that should also be sent to pharmacovigilance. The responsible will review the received form and will ask for additional information if needed. In the event of SUSAR, follow-up information will be provided.

SAE appearing more than 15 days from the end of the experimental therapy will be reported if the investigator considers there is a causal relationship to the therapy or if it is of medical importance.

#### *Notification of Laboratory Abnormalities*

All laboratory results must be filed in the subject's medical record and be monitored. The investigator must review laboratory results in a timely manner demonstrated by signature/date and assignment of clinical significance assessment. Laboratory abnormalities that are not clinically significant, i.e., minor deviations from the normal range, are expected and it is likely that no medical intervention will be required. Such results will not be considered to be adverse events.

#### *Clinically Significant (CS) Laboratory Abnormalities*

All CTCAE Grade 3 and 4 laboratory result abnormalities and any laboratory abnormality that is considered to be clinically significant by the investigator will be recorded on the AE case report form. An abnormal test result will be considered an AE if:

- It is not associated with an already reported AE, diagnosis or pre-existing condition
- There is a change in concomitant medication or intervention as needed, in direct response to the Grade 3 or 4 laboratory result
- The investigator exercises his/her discretion to make significance determinations for any subject laboratory result
- All such laboratory abnormalities will be repeated and assessed as soon as possible for "seriousness" by the investigator or licensed physician, and if they meet the regulatory definition of "serious", they will be reported as SAEs following regulatory and protocol requirements. Repeat laboratory tests may be run in order to monitor the result.

#### *Serious Laboratory Abnormalities*

Any laboratory abnormality meeting the regulatory definition of "serious" must be recorded both on the adverse event case report form and the Serious Adverse Event Form. If a subject experiences a serious toxicity or dies, the local and national required regulatory authorities will be notified within 24 hours of awareness of the event, as required.

#### ***Urgent or expedited notification of SUSAR to health authorities***

Responsible Pharmacovigilance person will notify all SUSAR to the AEMPS following the procedures approved by law. Any SUSAR will be reported within 15 calendar days from the moment when the sponsor has knowledge of it. Any fatal or life-threatening, SUSAR, should be reported within 7 days of the moment the sponsor had knowledge of it. The initial information should be completed, if possible, within 8 additional days.

